### Intervention plan

#### Intervention packages - behaviour change communication (BCC) through home-based counselling

The nutrition-specific BCC modules are adapted from the WHO-UNICEF published ‘Key messages booklet on the community infant and young child feeding counselling package’ [27] with linguistic help from the nationally adapted and validated BCC modules [28, 29]. The modules combine the three BCC types: i) Maternal nutrition during pregnancy; ii) Infant nutrition through exclusive breastfeeding; iii) Child nutrition through age-appropriate complementary feeding during 6–23 completed months. During pregnancy, counselling sessions include BCC on nutrition during pregnancy; and sensitization for WHO-recommended optimal breastfeeding practices. Starting immediately after birth of offspring to postnatal 5th month, intensive counselling and hands-on demonstrations are conducted every month of optimal breastfeeding practices (including positioning and attachment, expression and storage of breast milk), and nutrition of lactating mothers. From 6th month, counselling and hands-on demonstration sessions are conducted every three months and include preparation and feeding of optimal, age-appropriate and nutritious complementary food made from local ingredients, responsive feeding, continued breastfeeding, and nutrition of lactating mothers. Additional counselling visits are made if requested by respondents or if CHW deems the respondent is resistant to change their current practices. As integral parts of nutrition, counselling on good hygiene and care-seeking practices for both mother and child are also delivered in each session.

#### Intervention packages - nutritional supplementation

The prenatal and complementary food supplements being provided were previously tested in a supplement trial in Bangladesh [30], and are provided in selected clusters randomised to the three arms to receive either one or both supplements (Fig. 1).

#### Nutritional supplements for pregnant women

A lipid-based nutritional supplement (LNS) developed by Nutriset™, packed in ~20 g sachets, is provided to pregnant women. The formulation contains vegetable fat (soy), skimmed milk powder, peanuts, vitamin and mineral complex, sugar, stabilizer: fully hydrogenated vegetable fat, and antioxidant: tocopherols. An additional file details the components (see Additional file 1). Each sachet contains 70–75% of the recommended dietary allowance (RDA) for most of the micronutrients, and partial provision of protein and lipids, including essential fatty acids. The dose is one sachet per pregnant woman per day throughout pregnancy.

#### Complementary food supplements for children

Another LNS formulation developed by Nutriset™, packed in each ~10 g sachets, is provided to be fed to children from 6 to 23 completed months of age. The formulation contains vegetable fat, skimmed milk powder, peanuts, sugar, vitamin and mineral complex, maltodextrin, and emulsifier: lecithin. An additional file details the components (see Additional file 2). Each 20 g of LNS contains 70–75% of RDA for most of the micronutrients, and partial provision of protein and lipids, including essential fatty acids. The dose is two sachets per child per day, starting from 6 completed months of age (180 days) continued till 23 completed months.

### Comparison arm (natural practice)

In the comparison arm, study participants are receiving usual nutrition interventions available from routine health services only. Pregnant women are eligible to receive nutrition counselling on maternal and child nutrition during antenatal check-up (ANC) visits and caregivers of children under two years of age receives IYCF counselling during postnatal care visits within 42 days and sick child management visits at health facilities and by NGO workers (if available) [31]. However, contact coverage and content quality of these platforms and interventions is very low and does not reach those who do not seek the services. Antenatal iron-folic acid supplements are available during ANC contacts at public health facilities. Children aged 6–59 months receive vitamin A supplements during biannual national vitamin A campaigns, although coverage is unsatisfactory [11].

### Field implementation of interventions

Counselling and supplement sachets are delivered through our specially trained Community Health Workers (CHWs). Their tasks are supervised and monitored by two layers of field supervisors – a team of Field Supervisors (FSs), and a Field Research Assistant (FRA). Minimum educational qualification of the CHWs is Higher Secondary School Certificate (HSC) completed, while the FSs and the FRA have completed their Bachelor’s degree. The intervention team was given intense counselling training in three phases, and monthly meetings are held for field-related troubleshooting and as refresher courses. Supervisors provide daily feedback to associated CHWs during on-site counselling supervision.

At least 4 antenatal counselling sessions are delivered during pregnancy. Following live birth notification, 8 counselling sessions are delivered within 48 h and 7–14 days of birth, and at completion of every month till 6 months. Thereafter, counselling is delivered every third month till postnatal 23 completed months (Table 1). The CHWs also distribute supplement sachets every month, and provide counselling on the importance and instructions on supplement taking and storage.

### Evaluation plan

A range of quantitative data collection methods, including structured questionnaire and anthropometric measurements, have been adopted for assessments of primary and secondary outcomes. A timeline depicts the schedule of data collection in Table 2.

**Table 2 Tab2:**
[figure not shown]
Schedule of enrolment, interventions, and assessments of the study

*GA* Gestational age, *BCC* Behaviour Change Communication on Nutrition and health, *PNS* Prenatal Nutritional Supplementation, *CFS* Complementary Food Supplementation, *SES* Socio-economic status, *HFS* Household food security, *DD* Dietary diversity, *KAP* Knowledge, attitude and practice on nutrition, *WASH* Water, sanitation and hygiene, *IYCF* Infant and young child feeding, *MUAC* Mid upper arm circumference, *HC* Head circumference

### Trial outcomes and measurements

#### Primary outcomes

The primary outcome measure will be the LAZ of children at 24 months of age based on WHO MGRS 2006 child growth reference. This will be calculated from the child’s age in months and length on associated ages. Length is measured at age 7–10 days, then monthly from 1 to 6 months, and at 9^th^, 12^th^, 15^th^, 18^th^, 21^st^ and 24^th^ months of age, with locally manufactured collapsible length boards (precision 1 mm).

### Secondary outcomes

#### Gestational weight gain of mothers

Body weight of mothers is measured during enrolment and on the 6th and 9th month of gestation. Gain in weight will be compared among homogenous gestational ages and initial nutritional status of mothers. Weight is measured with a Tanita™ weighing scale (precision 100 g).

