### Cluster randomization and intervention allocation

We purposively selected two adjacent sub-districts (*Bahubal* and *Nabiganj*) of *Habiganj* district. These two sub-districts have a total of 20 unions (lowest administrative unit). We excluded 8 unions, 3 being in hard-to-reach areas (seasonal flooding and poor road transport system) and 5 having intensive nutrition intervention projects implemented by other non-government organisations (NGOs). The remaining 12 unions had enough population to cover the desired sample size. Each union was then divided into clusters, each cluster comprising of ~450 households or ~2000 population (average 2–3 villages). We selected five clusters or multiples of 5 clusters from each union, 125 clusters in total following the cluster exclusion criteria detailed in Table 1. We then applied block randomisation by generating random sequence of 1–5 (each number representing a specific study arm) of 25 blocks with the analytical software Stata SE 14.2. Clusters were then allocated to arms, five at a time, based on the random sequence (Fig. 2). Taking equal numbers of clusters per arm from each union will ensure neutralizing the effect of variations, if any, of background characteristics between the unions. Allocation concealment was impractical due to community-based study design and nature of BCC intervention. However, care is taken to keep the outcome assessors blinded to the interventions allocated to specific clusters. The intervention and the evaluation teams have minimal contact to minimise information bias.

**Table 1 Tab1:** Inclusion and exclusion criteria

Exclusion criteria for clusters	
• Similar nutrition interventions currently being implemented by either government or non-government agencies in the selected cluster • The cluster is too hard to reach • The cluster includes tea gardens. Communities in tea gardens comprise of unique ethnicity, culture and lifestyle for which our intervention is not customized.	
Inclusion criteria for participants	
• All newly identified pregnant women aged 15 to 49 years • Gestational age ≤ 125 days • Permanent residents of the study area.	
Exclusion criteria for participants	
• Woman could not recall last menstrual period (LMP). • Woman not a permanent resident of the study area

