#### Other measurements

Background characteristics of study participants: Information on demographic and socio-economic status (SES), family members, reproductive and morbidity history of pregnant women were collected using a structured questionnaire [25]. Household food security (HFS) information was collected through a questionnaire adapted from food security and nutrition surveillance tool [34]. These were recorded once during recruitment of the pregnant women after consent has been taken, to compare background characteristics between the arms.

Water sanitation and hygiene (WASH) and Knowledge attitude and practice (KAP): A questionnaire on the core indicators on water, sanitation and hygiene (WASH) was developed based on a standard manual for WASH [35]. Woman’s knowledge, attitude and practices (KAP) regarding maternal and child nutrition was developed based on WHO-recommended IYCF indicators and KAP manual [36]. WASH and KAP are collected during pregnancy and postpartum follow up visits.

Childhood morbidity: Morbidity, especially diarrhoea, directly impedes growth, while better hygiene practices lower infectious disease burden [37]. Therefore, children’s morbidity data is collected every month from postnatal 1 to 6 months and every three months thereafter till 24 months, using a 2-week recall questionnaire [11]. Vaccination data would be collected at 12 and 15 months based on EPI schedule.

Additional anthropometric measurements: Mother’s height is measured during recruitment for body mass index (BMI) calculation during early pregnancy. Mother’s mid-upper arm circumference (MUAC) (precision 1 mm), infant’s head circumference (during 1–6 moths age) and infant’s MUAC (during 7–24 months) are collected during follow-up visits, for associated z-score calculations.

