### Statistical analysis plan

Data analysis to detect change of the primary outcome (mean LAZ) will be conducted with length measured at 1, 3, 6, 9, 12, 15, 18, 21 and 24 months of age using t-tests assuming LAZ will satisfy the normality assumption. Longitudinal assessment of significance using lag time of stunting (mean length > −2SD below median of WHO reference population) will be done by the log rank test, followed by fitting a Cox proportional hazards model for each intervention arm to determine the change in risk of stunting compared to the comparison arm. Multiple linear regression will be employed to quantify the effect of intervention in each intervention arm compared to the comparison arm in terms of mean LAZ change and some secondary continuous outcome measures including changes in mother’s weight, birth weight, diarrhoea morbidity. Logistic regression will be used on binary outcome variables which comprise most of our secondary outcomes measures (e.g. – EBF and breastfeeding initiation within 1 h of birth). All these models will be controlled for possible confounders (household food security, educational background and SES) if randomisation of the clusters does not control for differences in these factors at baseline. For regression models, we shall consider random effects of clustering. All analysis will be intention-to-treat. Quantitative data analysis will be done using Stata SE 14.2 (StataCorp LP, College Station, Texas, USA).

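### The regression named for maternal weight change omits gestational age and initial nutritional status, the two factors on which the protocol says weight gain will be compared like with like

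*Protocol article*

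**What the plan says.** Gestational weight gain is the first secondary outcome listed in the protocol article. The measurement plan is "Body weight of mothers is measured during enrolment and on the 6th and 9th month of gestation", and the comparison is described in one sentence: "Gain in weight will be compared among homogenous gestational ages and initial nutritional status of mothers". No strata, cut-points, test or method of pooling is given.

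The *Statistical analysis plan* section assigns multiple linear regression to "some secondary continuous outcome measures including changes in mother’s weight, birth weight, diarrhoea morbidity", each intervention arm against the comparison arm. On covariates it says "All these models will be controlled for possible confounders (household food security, educational background and SES) if randomisation of the clusters does not control" for baseline differences in those factors. On clustering it says "For regression models, we shall consider random effects of clustering". Gestational age, enrolment weight and BMI do not appear in the list.

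Table 1 admits women at "Gestational age ≤ 125 days". *Other measurements* records that height is taken at recruitment "for body mass index (BMI) calculation during early pregnancy". *Participant recruitment* gives 10 women per intervention cluster and 20 per comparison cluster, found by door-to-door surveys repeated in monthly cycles, with LMP asked of each woman.

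**The concern.** The outcome section identifies two things that must be alike for weight gain to be compared fairly: gestational age and the mother's initial nutritional status. The regression that would estimate the effect names neither. An analyst following the analysis section would leave both out. An analyst following the outcome section would have to invent a way of bringing them in, and could reasonably choose anything from covariate adjustment to separate tests in subgroups.

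The follow-up weights are tied to gestational months, but the baseline weight is not. A woman weighed early in pregnancy has a longer period of gain counted than one weighed near day 125. Left out of the model, that difference goes into the error term. If gestational age at enrolment happened to differ between arms, it would also shift the estimated effect, and none of the three named covariates would correct it.

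**Working it through.** The article gives no effect size, SD, ICC or power for gestational weight gain, so there is no planned figure to reproduce. The figures below are illustrative, with assumptions marked.

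**1. The two sections side by side**

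| | Outcome section | Analysis section |
|---|---|---|
| Gestational age | must be alike | not named |
| Initial nutritional status | must be alike | not named |
| Food security, education, SES | not mentioned | only if unbalanced |
| Method | not stated | linear regression, random cluster effects |

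**2. Gain from adjusting for enrolment weight**

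Assume equal variance σ² at enrolment and follow-up, with correlation ρ.
- Variance of a change score: 2σ²(1 − ρ).
- Residual variance after adjusting for enrolment weight: σ²(1 − ρ²).
- Ratio: (1 + ρ)/2.

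For assumed ρ = 0.80, 0.90 and 0.95 the ratio is 0.90, 0.95 and 0.975. Variance therefore falls by 10%, 5% and 2.5%, and the standard error by about 5% at most (√0.90 = 0.949) and 1% at least (√0.975 = 0.987). The further gain from adjusting for the interval depends on the spread of gestational age at enrolment and the rate of gain, neither of which is given.

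**3. Cost if the outcome sentence were run as separate within-stratum tests**

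Inputs: 250 women per intervention arm, 500 in the comparison arm, 25 clusters per arm (*Sample size*; *Cluster randomization*). Assumed: all women measured, nine equal strata spread evenly over clusters, ICC 0 or 0.06. The value 0.06 is the protocol's figure for HAZ; none is given for maternal weight.

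SE in SD units = √(DEᵢ/nᵢ + DE_c/n_c), with DE = 1 + (m − 1) × ICC and m women per cluster.
- Whole arms, ICC 0: √(1/250 + 1/500) = 0.077.
- Whole arms, ICC 0.06: DE = 1.54 (m = 10) and 2.14 (m = 20); √(1.54/250 + 2.14/500) = 0.102.
- One stratum of nine (27.8 v 55.6 women), ICC 0: 0.077 × √9 = 0.232.
- One stratum of nine, ICC 0.06: DE = 1.007 (m = 1.11) and 1.073 (m = 2.22); √(1.007/27.8 + 1.073/55.6) = 0.236.

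The SE ratio is 3.0 at ICC 0 and 0.236/0.102 = 2.3 at ICC 0.06. Multiplying by 1.96 + 0.84 = 2.80, the difference detectable with 80% power at two-sided 5% rises from 0.22–0.29 SD to 0.65–0.66 SD.

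**4. Could gestational age at enrolment differ by arm?**

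*Sample size* gives 23 live births per 1000 and 2000 people per cluster, or 46 a year. Assume detection from day d = 28 to 45, consent c = 85–100%, sweeps every 30 days, births standing in for pregnancies, and quotas filled strictly in order of detection.
- First sweep yield: (46/365) × (125 − d) × c, which is 8.6 (d = 45, c = 0.85) to 12.2 (d = 28, c = 1). This nearly or fully fills a quota of 10 but only about half of a quota of 20.
- Mean gestational age: (125 + d)/2 for women found in the first sweep, about d + 15 for those found later.
- Example, d = 28, c = 0.85: yield 10.4. Intervention mean 76.5 days; comparison mean (10.4 × 76.5 + 9.6 × 43)/20 = 60.4 days; gap 16 days.
- Example, d = 45, c = 0.85: yield 8.6. Intervention mean (8.6 × 85 + 1.4 × 60)/10 = 81.5 days; comparison mean (8.6 × 85 + 11.4 × 60)/20 = 70.8 days; gap 11 days.

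If enrolment was spread evenly over the window in every cluster, the gap would be near 0. The article does not state the fill order, so the range is 0 to about 16 days.

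**The case against.** The strongest reply is that the two sections can be read together. The covariate list is generic: it serves LAZ, birth weight, diarrhoea and the feeding outcomes alike. Gestational age and initial nutritional status matter specifically for weight gain, so it is natural to mention them under that outcome. On this reading the authors recognised both factors and the detail was left to a fuller document.

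Much of this stands. A reader might infer that the protocol commits to cell-by-cell testing, but the text sets no cells, cut-points or per-cell tests, so the nine strata above are an illustration. A pooled stratified estimate is not excluded and would lose little precision. Nor do the documents support calling these the strongest predictors of gain; by the calculation above, enrolment weight alone removes at most about 10% of the variance at the assumed correlations.

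A reader might also infer that the planned comparison is biased. That is not shown. Eligibility rules and monthly sweeps are described the same way for all arms, the later weights are fixed to the 6th and 9th months, and under cluster randomisation the omission mainly costs precision. The route through unequal quotas depends on a fill order that the article does not describe.

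What does not stand is that nothing needs changing. The analysis section applies a named covariate list to all its models, and that list does not carry out what the outcome section calls for. This goes beyond unstated detail: both sections describe the analysis of the same outcome, and they do not meet.

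**Conclusion.** The point holds as a modest one. The regression as written does not implement the like-with-like comparison promised for gestational weight gain, and the outcome section does not say how that comparison will be made. The two sections need to be aligned; they are not irreconcilable.

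The calculable gain from adjusting for enrolment weight is a 2.5–10% reduction in variance against a plain change score, resting on an assumed correlation of 0.95–0.80 and equal variances. The gain from adjusting for the interval comes on top and cannot be computed from the article. Separate within-stratum tests would cost far more, with SEs about 2.3–3 times larger for an assumed nine strata, but the protocol does not commit to them. A difference in gestational age between arms is a possibility to guard against, not a demonstrated bias. The outcome is secondary and the primary LAZ analysis is untouched.

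**What to change.** In the *Statistical analysis plan* section, state that for maternal weight the regression with random cluster effects always includes enrolment weight (or early-pregnancy BMI), gestational age at enrolment and gestational age at measurement, whether or not they look unbalanced. In *Gestational weight gain of mothers*, say that this adjustment is how the comparison at like gestational age and nutritional status is made. Label any comparison within strata exploratory.

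The regression already planned is enough; a more elaborate model with union and woman-level effects is not needed to settle this point. Gestational age at measurement is recorded after randomisation, but visits are generated on a preset schedule, so adjusting for it should be harmless provided visit timing is similar across arms; that can be checked in the data.

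The cost is wording and three model terms. Weight, height and LMP are already collected.

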#### Weight of children

Body weight of children is measured at birth, on 7–10 days, then monthly from 1 to 6 months, and every third month thereafter till 24 month, using Salter scales (precision 10 g).

##### Nutritional intake of mothers

Detailed ingredients of the pregnant mothers’ dietary intake on the previous 24-h are collected, through an interviewer-administered open 24-h dietary recall form adapted from the FAO dietary diversity guidelines [32], during enrolment and on the 6th and 9th month of gestation. Further, maternal food intake is collected every third month after birth till 24 months. Ingredients will be collated into food groups to calculate dietary diversity score.

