### Project management system for implementation and monitoring

A bespoke automated Project Management Information System (MIS) has been developed linking data collection and intervention delivery through android-based tablet (handheld)-PC with a central database where progress can be monitored by the field supervisors and central staff. On pregnancy enrolment through the tab, an android platform-based application automatically generates subsequent prenatal visit plans and tools at pre-specified schedules and tasks of CHWs and data collectors (intervention modules for CHWs and questionnaire for data collectors). Similarly, birth is registered in the tab immediately upon notification. To ensure post-partum data collection within 24 h of delivery, a mobile phone-based birth-notification system has been established. Enrolled pregnant women and their family members are continuously encouraged to notify birth by text message or voice calls as early as possible, preferably within six hours of birth. Registration of live births then generates appropriate plans and tools for postpartum visits by CHWs and data collectors. The web-linked desktop dashboard system is used to monitor activities/performance of CHWs and data collectors in real time by field supervisors and the central team.

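### The enrolment dietary diversity score is collected but is missing from the covariates stated for all models, so the maternal diet comparisons give up some precision

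*Protocol article*

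**What the plan says.** Under Nutritional intake of mothers, the protocol article describes a 24-hour recall form "adapted from the FAO dietary diversity guidelines [32], during enrolment and on the 6th and 9th month of gestation". It continues: "Further, maternal food intake is collected every third month after birth till 24 months", and "Ingredients will be collated into food groups to calculate dietary diversity score". The outcome is therefore scheduled once at enrolment, twice later in pregnancy, and repeatedly after birth.

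The Statistical analysis plan section assigns multiple linear regression to the primary outcome and to "some secondary continuous outcome measures including changes in mother’s weight, birth weight, diarrhoea morbidity", and logistic regression to binary outcomes. It then sets one adjustment rule: "All these models will be controlled for possible confounders (household food security, educational background and SES"), to be applied "if randomisation of the clusters does not control for differences in these factors at baseline". Random effects of clustering are planned for the regression models. Dietary diversity is not named in that section.

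For the other maternal outcome measured at the same three pregnancy visits, the article does bring in the starting point: "Gain in weight will be compared among homogenous gestational ages and initial nutritional status of mothers".

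**The concern.** The enrolment value of an outcome is usually the covariate most closely related to its later values. Here it is already in the data collection schedule, yet the covariate rule covers three background factors only. The trigger for adjustment also refers only to those three. A team that follows the section literally would leave the enrolment diet score out, even if it differed visibly between arms.

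What is at stake is the width of the intervals for the effect of the intervention bundles on maternal diet, an effect that the Discussion says the trial will explore. Writing the term in beforehand also avoids having to decide on it after the arms have been seen to differ at enrolment.

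**Working it through.** **The plan's own figure.** No sample size or power is given for maternal diet. The stated 175 children per arm concerns LAZ. It reproduces as 2 × ((1.96 + 0.842)/0.4)² = 98.1, times a design effect of 1 + 13 × 0.06 = 1.78, which gives 174.6, so 175. The 14 children per cluster used here is 350/25 in the comparison arm; the article does not say that this was the value used. The figure neither supports nor weakens the present point.

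**Inputs from the article.** 250 women per intervention arm and 500 in the comparison arm; 10 and 20 per cluster; 25 clusters per arm.

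**Assumptions, not in the article.** ICC for diet 0.06 (borrowed from the HAZ value; range 0.02 to 0.10). Correlation r between enrolment and follow-up scores 0.2 to 0.5. Two-sided 5% test. Scores in SD units.

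**Step 1: size of ordinary chance differences at enrolment.** The design effects are 1 + 9 × 0.06 = 1.54 and 1 + 19 × 0.06 = 2.14.

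SE = √(1.54/250 + 2.14/500) = √0.01044 = 0.102 SD.

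So 95% of chance differences lie within about ±0.20 SD. With ICC 0.02 to 0.10 the SE is 0.086 to 0.116.

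**Step 2: share carried into an unadjusted follow-up comparison.** This is r times the enrolment difference: 0.02 to 0.05 SD for a one-SE difference, and 0.04 to 0.10 SD at the 95% limit.

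**Step 3: gain from adjustment.** The variance is multiplied by about 1 − r², and the interval width by √(1 − r²). The last column gives the power for a difference that has 80% power without adjustment, (1.96 + 0.842) × 0.102 = 0.29 SD.

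| r | Variance saved | Interval narrower by | Power |
|---|---|---|---|
| 0.2 | 4% | 2% | 82% |
| 0.3 | 9% | 5% | 84% |
| 0.4 | 16% | 8% | 86% |
| 0.5 | 25% | 13% | 90% |

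The percentage savings depend on r and not on the number of women, so losses after enrolment do not change them.

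**Limits of the formula.** 1 − r² uses a single correlation; in a cluster trial the gain depends on the between-cluster and within-cluster correlations separately. It also applies to a continuous score. If the score is dichotomised and modelled by logistic regression, these percentages do not carry over.

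**The case against.** The strongest reply is that this is silence and not a decision. The section never names dietary diversity, its list of continuous outcomes is open-ended, and an unseen analysis plan could add the term. The sentence on confounders can be read as a rule for background factors, with no intention of excluding outcome baselines; the treatment of maternal weight suggests that the authors use a starting value where they describe one. This is right as far as it goes, and it keeps the point small. It does not remove it, because the section fixes a covariate list for all its models and makes even that list conditional.

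Several stronger readings are tempting and are not supported:

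- A reader might infer that raw follow-up scores will be compared, or that the two later pregnancy recalls will not be combined. The article states neither.
- A reader might infer that chance differences in diet bias the estimates. Under randomisation they do not, on average, and the planned cluster random effects give intervals that already allow for them. This presumes that recruitment within clusters did not depend on arm; the article reports no such dependence.
- A reader might take the enrolment recall as a known pre-intervention value for every woman. The timing is an inference from "On pregnancy enrolment through the tab, an android platform-based application automatically generates subsequent prenatal visit plans", since the schedule table is not legible here, and completeness of the recall is not stated.
- A warning against change scores would answer a plan that nobody has stated for diet.

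It is also fair to say that r is likely to be low. Each score rests on one day's intake, and the last postpartum recall comes more than two years after enrolment.

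**Conclusion.** The point holds as a minor, nearly free improvement for a secondary outcome. Followed as written, the covariate rule leaves an already scheduled baseline of the outcome unused. The loss is one of precision: about 4 to 25% of the variance for an assumed r of 0.2 to 0.5, with the lower end more plausible for single-day recalls in pregnancy and lower values still after birth. At r = 0.2 the interval narrows by only about 2%. Nothing here threatens validity, and the primary outcome is unaffected. The conclusion rests on the enrolment recall preceding intervention, on dietary diversity falling under the models of the Statistical analysis plan section, and on no separate document adding the term.

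**What to change.** Add to the Statistical analysis plan section, before the diet data are analysed:

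> The enrolment dietary diversity score will be a covariate in every model of maternal dietary diversity (linear, or logistic if the score is dichotomised), together with the planned cluster random effect, whatever the observed baseline balance. Women without an enrolment recall will be retained by setting the score to the overall enrolment mean across arms and adding a missing indicator.

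Either mean imputation or a missing indicator would serve as the rule for missing enrolment values; what matters is that it is fixed beforehand and does not depend on arm. A joint repeated-measures model of the 6th- and 9th-month scores is optional and not needed for this point.

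The cost is one or two sentences and no new data. If logistic regression is used, the report should say that the odds ratio is conditional on the enrolment score.
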